# FAIRY: a randomized controlled patient-blind phase III study to compare the efficacy and safety of intravenous ferric carboxymaltose (Ferinject®) to placebo in patients with acute isovolemic anemia after gastrectomy - study protocol for a randomized controlled trial

**DOI:** 10.1186/1745-6215-15-111

**Published:** 2014-04-05

**Keywords:** Ferric carboxymaltose, Isovolemic postoperative anemia, Gastric cancer, Randomized controlled trial

## Abstract

**Background:**

Isovolemic anemia (decrease in hemoglobin concentration with normal or even increased blood volume) after gastric cancer surgery may negatively influence short- and long-term outcomes. Therefore correction of isovolemic postoperative anemia is supposed to be beneficial. This prospective randomized placebo-controlled multicenter trial is designed to evaluate the efficacy of ferric carboxymaltose administration with the primary end point of successful hemoglobin level increase by 2 g/dl at 12 weeks after randomization.

**Methods and design:**

Gastric cancer patients after oncologic resection and postoperative hemoglobin level ≥ 7 g/dl to <10 g/dl at postoperative days 5 to 7 will be eligible for trial inclusion. After randomization, 450 patients (225 per group) are going to be subjected either to administration of ferric carboxymaltose (treatment group) or normal (0.9%) saline (placebo group). Patients will be blinded to the intervention. Patients will undergo evaluation for hemoglobin level, hematology and quality of life assessment 3 and 12 weeks after randomization.

**Discussion:**

Correction of isovolemic postoperative anemia in gastric cancer patients after oncologic resection is considered to be beneficial. Administration of ferric carboxymaltose is considered to be superior to placebo for anemia correction without the possible risks of red blood cell transfusion. Further, improved quality of life for patients with quick recovery of hemoglobin levels is expected.

**Trial registration:**

NCT01725789 (international: http://www.clinicaltrials.gov) and NCCCTS-12-644 (NCC, Korea).

## Background

Perioperative anemia occurs in 25% to 75% of cancer patients, and the prevalence of anemia in the immediate postoperative period after major surgery is as high as 90%
[1,2]. Postoperative acute isovolemic anemia (decrease in hemoglobin concentration with normal or even increased blood volume) can affect the recovery and quality of life (QoL) of patients by subtly slowing the reaction time, deteriorating memory, increasing heart rate, and decreasing oxygen levels
[3,4]. It has been suggested that low hemoglobin levels may affect oncologic outcomes in gastric cancer patients
[5,6]. Jung et al. revealed that low hemoglobin levels were related to postoperative complications
[5]. Further, it was demonstrated that postoperative anemia resulted in decreased overall survival
[6]. Therefore correction of postoperative anemia is an important issue. However, transfusion guidelines and patient blood management programs are not commonly implemented so far. This is reflected by the fact that postoperative transfusion rates for colorectal and gastric cancer patients were reported to be 10% to 38%
[7,8]. It was demonstrated before that transfusion of red blood cells (RBC) carries substantial risks for patients and may even worsen postoperative oncologic longterm outcome
[9,10]. Those risks may be acute hemolytic reactions, transfusion-related acute lung injury, immunization events, organ dysfunctions, and failures and the possibility of incorrect transfusions. The best evidence so far is derived from a meta-analysis for red blood cell transfusions in colorectal cancer patients which concludes that RBC transfusion is related to higher cancer recurrence and decreased survival rates
[11]. This data was also confirmed for other tumor entities such as pancreatic cancer and hepatocellular carcinoma
[12,13]. Therefore alternative procedures to classical RBC-transfusion should be considered of highest interest. Iron supplementation may be a conceivable alternative. However, oral iron intake was reported to be related to a considerable amount of side effects
[14] which can be hypersensitivity, paresthesia, hypotension, dyspepsia, vomiting, abdominal pain, myalgia/arthralgia, and pyrexia. Further, dietarian supplementation may be hampered by substantially affected resorption from the GI-tract after gastric cancer surgery
[14]. Therefore intravenous iron supplementation is a substantial alternative. However, iron dextran infusion is considered to be rarely related to potentially life-threatening side effects
[15]. Alternatively ferric carboxymaltose was proposed to be safer regarding the common side effects of intravenous (iv-) iron infusion
[15].

In a retrospective observational study performed at the sponsor site the role of intravenous iron was assessed before
[16]. Postgastrectomy patients treated with iron sucrose had a faster and more complete Hb-response compared to untreated patients and none of the treated patients developed chronic anemia 12 months after surgery. Further, no adverse events related to iron infusion were noted. However, selection bias could not be ruled out in this study, because in this retrospective analysis the percentage of advanced gastric cancer patients treated by intravenous iron was higher than in the non-treated group. Therefore we propose this randomized placebo controlled phase III trial in order to evaluate the efficacy and safety of intravenous ferric carboxymaltose supplementation for correction of postoperative isovolemic anemia in gastric cancer patients.

## Methods

### Study population, inclusion, and exclusion criteria

All patients with a hemoglobin-level ≥ 7 g/dl to <10 g/dl at postoperative days 5 to 7 after oncologic gastrectomy for gastric cancer will be eligible for screening. All patients aged 20 years and over and willing to give informed consent will be eligible. Participation in another trial interfering with the outcome of this study, language problems, lack of compliance, mental inability, unstable angina or myocardial infarction within 6 months of the trial, severe respiratory disease, ASA (American Society of Anesthesiologists) Score >3, inadequate liver, kidney, and bone-marrow functions (evaluated by measurement of white blood cell count (WBC), platelets, aspartate aminotransferase (AST), alanine aminotransferase (ALT), C-reactive protein (CRP), and creatinine), pregnancy/lactation, and Eastern Cooperative Oncology Group (ECOG) status >1 will be considered unspecific exclusion criteria. Further, patients with a known history of hypersensitivity or allergy to ferric carboxymaltose, active inflammatory disease (surgical, site infection, pneumonia, Systemic Inflammatory Response Syndrome (SIRS)), history of previous erythropoietin or iv-iron administration within 4 weeks prior to screening, history of iron overload (hemochromatosis) and anemia due to reasons other than iron deficiency will not be eligible for this trial. The study protocol was approved by the Institutional Review Board (IRB) of the National Cancer Center Korea on 7 November 2012 (NCCCTS-12-644). All participating centers approved the trial by their local IRBs subsequently. Further, the trial was registered in the clinical trials database (NCT01725789) (Figure 
1).

**Figure 1 F1:**
[figure not shown]
Study scheme of FAIRY trial, inclusion/exclusion criteria, intervention, and end points.

### Procedures

#### General procedures

After consenting to participate in the trial, patients will be randomized to either one of the two treatment groups (500 to 1,000 mg ferric carboxymaltose (Ferinject®) *vs.* placebo (0.9% saline)). After inclusion of eligible patients medical history will be taken and all concomitant diseases and medications will be recorded. All trial participants will receive routine examination and blood testing for the following parameters: hemoglobin, RBC, WBC, platelets, serum ferritin, transferrin saturation, AST, ALT, CRP, and creatinine.

#### Assessment of quality of life

Quality of life (QoL) as one of the most important secondary endpoints will be assessed by standardized European Organization for Research and Treatment of Cancer (EORTC) QLQ C-30, and STO-22 (EORTC Study Group on Quality of Life) questionnaires, which are already broadly established and validated. Crawford and Cella
[17] reported that the maximal incremental gain in QoL occurs when the hemoglobin level lies in the range of 11 to 13 g/dL. Differences in QoL were even noted when the Hb-level was only 1 g/dL lower. Therefore we hypothesize that rapid Hb-nomalization by intravenous iron administration may improve QoL. As such, QoL will be assessed at multiple time points postsurgery during the follow-up visits.

#### Intervention

The treatment group will be administered ferric carboxymaltose (1,000 mg for bodyweight ≥50 kg or 500 mg for bodyweight <50 kg (maximum dose of ferric carboxymaltose: 20 mg/kg)) as iv-drip infusion over an administration time of at least 15 (1,000 mg) or 6 (500 mg) min. All patients with a serum ferritin level of <15 ng/mL and Hb-level <10 g/dl at postoperative week 3 will receive a second administration of 500 mg ferric carboxymaltose as described above. The placebo group will receive normal saline (0.9%) as iv-drip infusion (200 mL for bodyweight ≥50 kg or 100 mL for bodyweight <50 kg) over an administration time of at least 15 (200 mL) or 6 (100 mL) min. During infusion patients will be blinded.

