### Safety

Stopping rules of the study medication will not apply due to a single administration of ferric carboxymaltose. However, in case of hypersensitivity or anaphylactic reactions immediate interruption of infusion will be mandatory. Further management will be left to the discretion of the physician on duty. Any (serious) adverse event ((S) AE), any (unexpected) (serious) adverse drug reaction, and any suspected unexpected serious adverse reaction (SUSAR) will be documented. All SAEs, SADs, and SUSARs will have to be documented and reported to the IRB by the responsible investigator according to local regulations.

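### Safety waives stopping rules because ferric carboxymaltose is given once, but Intervention orders a conditional second dose and does not say in which arm

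*Protocol article*

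**What the plan says.** **Second dose.** The protocol article, Intervention, gives the treatment group 1,000 mg FCM (bodyweight ≥50 kg) or 500 mg (<50 kg). It then adds: "All patients with a serum ferritin level of <15 ng/mL and Hb-level <10 g/dl at postoperative week 3 will receive a second administration", the dose being 500 mg FCM.

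**Placebo.** The next sentence begins "The placebo group will receive normal saline (0.9%) as iv-drip infusion" and sets 200 mL or 100 mL by weight, over at least 15 or 6 minutes. It mentions no repeat. The section closes with "During infusion patients will be blinded".

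**Stopping.** Safety states: "Stopping rules of the study medication will not apply due to a single administration of ferric carboxymaltose". It continues that "in case of hypersensitivity or anaphylactic reactions immediate interruption of infusion will be mandatory" and then "Further management will be left to the discretion of the physician on duty".

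**Entry.** The eligibility section excludes "patients with a known history of hypersensitivity or allergy to ferric carboxymaltose".

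**What blinding is for.** Methods against bias relies on patient blinding to protect the QoL assessment. Secondary endpoints ranks QoL among the most important secondary outcomes and measures it at 3 and 12 weeks.

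**The concern.** Two separate things are at stake.

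- **Safety rationale.** The waiver of stopping rules rests on one stated premise, a single exposure. That premise fails for exactly the patients who are exposed twice. A reaction to the first infusion is the main reason to withhold a second, and the text shown does not connect the two.
- **Comparability of the arms.** A repeat infusion is defined only as active drug, with no saline counterpart, and the sentence does not name an arm. Depending on how a site reads it, either the extra infusion marks the FCM arm before week-12 QoL is collected, or some controls receive the test drug before the primary endpoint at week 12.

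**Working it through.** **1. Number of administrations, side by side.**

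| Section | FCM administrations |
|---|---|
| Intervention | One, plus 500 mg more if ferritin <15 ng/mL and Hb <10 g/dl at postoperative week 3 |
| Safety | One |

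Both cannot hold for a patient who meets the rule. Total exposure if re-dosed:
- ≥50 kg: 1,000 + 500 = 1,500 mg (+50%)
- <50 kg: 500 + 500 = 1,000 mg (+100%)

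These sums describe exposure, not risk.

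**2. A patient who reacts to the first infusion.** The entry exclusion applies before dosing. The mandatory step is to interrupt the running infusion. What follows is left to the physician on duty. Three weeks later the re-dosing rule is worded as an instruction, without an exception. A physician may withhold the dose under the discretion clause, but no rule shown says so.

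**3. Which arm is re-dosed?**

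*Reading A, FCM only.* The sentence stands between the FCM and placebo regimens and speaks of a second FCM administration. Placebo patients, having had none, cannot have a second. On this reading only FCM patients are infused again. Masking during infusion hides what is infused, not that an extra infusion takes place. Disclosure further requires that patients can infer the rule. The week-3 QoL is little exposed; the week-12 QoL follows the repeat infusion.

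*Reading B, both arms.* The sentence refers to all patients, while the sentences around it name an arm. A second infusion then reveals nothing, but qualifying controls receive FCM. To see the scale, first reproduce the planned size:

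n per group = (1.960 + 1.282)² × [0.60×0.40 + 0.75×0.25] / 0.15² = 10.507 × 0.4275 / 0.0225 = 199.64, so 200 per group and 400 in total, as stated. Power at 200 per group (normal approximation, pooled variance under the null) is 89.6%.

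Now assume that a share q of controls is re-dosed. In the mild case they respond at 75% instead of 60%, so the control rate is 0.60 + 0.15q. In the extreme case all of them would otherwise have failed, so it is 0.60 + 0.75q.

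| q (assumed) | Mild: control rate | Power | Extreme: control rate | Power |
|---|---|---|---|---|
| 2% | 60.3% | 88.4% | 61.5% | 82.9% |
| 5% | 60.75% | 86.5% | 63.75% | 68.6% |
| 10% | 61.5% | 82.9% | 67.5% | 38.1% |

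The article gives no q. These rows illustrate Reading B only and are not forecasts.

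**4. Timing.** The trigger is at postoperative week 3. Screening Hb is taken on postoperative days 5 to 7, and the follow-up visit is 3 weeks (±7 days) after the intervention. If the infusion is given on the screening day, the nominal visit falls on postoperative day 5 + 21 = 26 to 7 + 21 = 28. The trigger and the visit are therefore on different clocks, and a fix has to name one.

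**5. Counts.** 1% of 225 = 2.25 patients per arm; 10% of 225 = 22.5.

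**The case against.** The strongest reply has four parts.

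- **Condensed article.** Criteria for withholding a dose after a reaction usually sit in the full protocol, which is not shown. Exclusion of known hypersensitivity, mandatory interruption and physician discretion all point towards withholding. This largely stands: a reader might infer that the trial requires re-exposure of patients who reacted, and the text does not support that. What remains is a stated reason that is wrong, which is not an omission.
- **Ambiguity.** The unblinding argument needs Reading A. That is correct, and it cannot be asserted as the only reading. Reading B does not rescue the text, because it exchanges disclosure for dilution.
- **Few re-doses.** Both criteria must be met together, and in the FCM arm this is after 500 to 1,000 mg of iv iron. The Discussion reports consistent replenishment of iron stores and Hb improvement usually within 2 weeks. This stands as a reason to expect few repeat infusions in that arm.
- **Dose range.** A reader might also see a contradiction in General procedures, which describes the regimen as "500 to 1,000 mg ferric carboxymaltose". It is a label for the initial weight-based dose and does not claim to be a cumulative maximum, so nothing should be built on it.

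**Conclusion.** The conflict between Intervention and Safety is explicit and needs no assumption: the reason given for waiving stopping rules is false for every re-dosed patient. It should be corrected. The missing exception after a reaction is a weaker point, since discretion may cover it in practice and the full protocol may address it.

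The arm ambiguity is real under either reading, but its size is unknown. The trigger rate is not given, disclosure depends on patients inferring the rule, and dilution arises only on the less natural reading. The effect is likely small.

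A reader might infer that blinding has failed, that QoL is biased, or that the primary comparison is compromised. The document does not support any of these. On Reading A the primary endpoint is a laboratory Hb value and is little affected. The sample size calculation reproduces and is not in question.

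**What to change.** 1. **Safety.** Replace the single-administration rationale. State that a second 500 mg dose is possible, and that no second infusion is given after a hypersensitivity or anaphylactic reaction to the first.
2. **Intervention.** State that the ferritin and Hb rule is assessed in both arms at the same visit, the 3-week post-intervention visit. FCM patients who qualify receive 500 mg FCM. Placebo patients who qualify receive a masked 100 mL saline infusion over at least 6 minutes, the volume and time that the weight rule already pairs with 500 mg. Hb and ferritin belong to the blood panel repeated at that visit, so no extra test is needed.
3. **If FCM for both arms was intended,** say so and label it as rescue.

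**Cost.** A short amendment, applied prospectively because recruitment has begun, and about 2 to 23 saline infusions if an assumed 1% to 10% of 225 placebo patients qualify. Those infusions bring the patients no benefit. Qualifying placebo patients would not receive study FCM, which is a real loss if the rule was meant for both arms; alternative anemia management remains open to them. No extra patients are needed.

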#### Follow-up

Follow-up visits will take place at 3 and 12 weeks (±7 days) after the study intervention. On the follow-up visits patients will undergo blood testing and QoL evaluation as described above.

### Study objectives

#### Primary endpoint

The primary efficacy endpoint will be the number of responders defined as an increase of the hemoglobin level of at least 2 g/dl related to the baseline hemoglobin measured after randomization at 12 weeks after administration of either placebo or ferric carboxymaltose.

#### Secondary endpoints

Major secondary endpoints will be: percentage of patients with Hb ≥10, 11, and 12 g/dL at 3 and 12 weeks (independent of alternative anemia management including transfusion or use of erythropoietin stimulating agents), percentage of patients requiring alternative anemia management therapy, average time-to-response (Hb increase ≥2 g/dL and/or Hb ≥10 g/dL) (independent of alternative anemia management including transfusion or use of erythropoietin stimulating agent, development of Hb, ferritin, and transferrin saturation over the study duration (12 weeks) independent of alternative anemia management including transfusion or use of erythropoietin stimulating agents and finally safety/tolerability of ferric carboxymaltose. QoL as one of the most important secondary endpoints will be assessed by EORTC QLQ C-30 and STO-22 questionnaires at 3 and 12 weeks.

### Methods against bias

Randomization into two treatment groups will be performed in order to omit selection bias from this trial. Randomization will be performed as block randomization in fixed block sizes in a 1:1 allocation ratio using a centralized web-based randomization system (eVelos (http://eresearch.ncc.re.kr/eres/jsp/ereslogin.jsp)). In order to achieve equal group sizes randomization will be stratified for each respective center (six centers). Further, patients will be stratified according to the need of adjuvant chemotherapy depending on the surgical/pathological stage (adjuvant CTx in patients with clinical/surgical/pathological stages II to IV according to UICC/AJCC
[18]). Patient blinding will rule out possible influences on QoL assessment. Patients and observers for postoperative outcomes will be blinded to guarantee an optimal study outcome. Potential confounding will be reduced by the randomization process.

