### Sample size calculation, statistical considerations, and trial feasibility

The sample size is based on a superiority design assuming a response rate to ferric carboxymaltose of 75% (per primary endpoint definition) by week 12. A response rate of 60% is assumed in the control group. This results in a 15% advantage for the treatment group which is considered medically meaningful. In order to achieve a statistically significant result with 90% power at a significance level of α = 0.05, 400 patients are required to be randomized according to the Pocock formula
[19]:

$$n=f\left(\alpha ,\beta \right)\times \left[p1\times \left(100-p1\right)+p2\times \left(100-p2\right)\right]/{\left(p2-p1\right)}^{2}$$

where p1 and p2 are the response rates in the control and experimental groups, respectively, and f(α, β) = [*Φ*^- 1^(α/2) + *Φ*^- 1^(β)]^2^.

To account for potential patient drop-outs over the 12-week study period, the sample size is estimated at 450 patients (225 per group). Although this number appears to be rather high, recruitment should be accomplished within several months. Each of the six participating centers treats at least 500 patients for gastric cancer every year which sums up to a volume of 3,000 patients per year. Based on the assumption of an incidence rate of 15% for postoperative anemia (18% in the sponsor’s institution) 400 patients may be recruited within one year.

The outcome parameters will be analyzed by a Pearson chi-square test or Fisher’s exact test (patient age and gender, clinicopathologic data, and morbidity) and Student’s t-test (Hb-level before treatment and hospital days after treatment). The Z-test will be used to determine whether or not a significant difference exists between two groups during follow-up.

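### Fixed block sizes in a trial that blinds only patients and outcome observers could let site staff know some allocations in advance

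*Protocol article*

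**What the plan says.** Under Methods against bias, the protocol article gives the purpose of randomising: "Randomization into two treatment groups will be performed in order to omit selection bias from this trial". The method follows: "Randomization will be performed as block randomization in fixed block sizes in a 1:1 allocation ratio using a centralized web-based randomization system". Two stratification factors are named. One is centre, with six levels. The other is chemotherapy need: "Further, patients will be stratified according to the need of adjuvant chemotherapy depending on the surgical/pathological stage".

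On blinding, the same section says: "Patients and observers for postoperative outcomes will be blinded to guarantee an optimal study outcome". The title calls the trial "a randomized controlled patient-blind phase III study", and the Intervention section adds only: "During infusion patients will be blinded". No sentence says that staff who recruit, randomise, prepare or give the infusion are blinded. No sentence says that the block size varies or is withheld from sites.

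The section on study population lists exclusions. Several are laboratory values or scores, but some carry no threshold in the article: poor compliance, mental inability, active inflammatory disease, and anaemia from a cause other than iron deficiency.

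**The concern.** With permuted blocks of constant size, the two arms come back into balance at the end of every block. Anyone who sees past assignments in one centre and stratum can eventually recognise that rhythm. Once one arm has used up its places in a block, the remaining assignments are known before the next patient is approached. A central web system hides the list, but it does not hide a pattern that can be read from past assignments.

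If the person who judges eligibility holds that knowledge, the judgement-based exclusions allow a patient to be taken or passed over according to expected haemoglobin recovery. An objective endpoint and blinded outcome observers give no protection, because the selection happens before treatment. The Background section explains why this matters here: selection bias could not be ruled out in the sponsor site's retrospective study, and the article gives that as its reason for a randomised trial.

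**Working it through.** **Inputs.** From Methods against bias: fixed blocks, 1:1, six centres and two chemotherapy levels. From the sample size section: 450 patients, from 400 before drop-out, with 75% against 60% response. Block size is not stated, so sizes 4, 6 and 8 are assumed as a range.

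**The plan's own figure.** The article gives no predictability figure. Its sample size reproduces: f = (1.960 + 1.282)² = 10.507, and n = 10.507 × (0.60 × 0.40 + 0.75 × 0.25) / 0.15² = 199.6 per arm, so 400. Nothing in this point changes it.

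**Strata.** 6 × 2 = 12, and 450 / 12 = 37.5 patients on average. That is about 9 blocks of size 4, 6 of size 6, or 4 to 5 of size 8.

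**Allocations certain in advance, block size known.** Block size 4 has six equally likely sequences. AABB and BBAA each fix two assignments in advance; the other four fix one each. That is (2 × 2 + 4 × 1) / (6 × 4) = 8/24 = 33%. For a block of size 2b the share is 1/(b + 1), which agrees with full enumeration.

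**Best guess.** Always guessing the arm with more places left is right with frequency [b + (4^b / C(2b, b) − 1)/2] / 2b. For b = 2 this is [2 + (16/6 − 1)/2] / 4 = 0.708.

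| Assumed size | Certain in advance | Of 450 | Best guess correct |
|---|---|---|---|
| 4 | 33% | 150 | 71% |
| 6 | 25% | 112.5 | 68% |
| 8 | 20% | 90 | 67% |

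Simple randomisation would give 0% and 50%. The table is an upper range, because it takes the size as known from the first patient.

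**Effect of varying the sizes.** This was simulated with 4,000 runs and 38 patients per stratum. The observer knows which sizes are possible but not which was drawn.

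| Design | Certain in advance | Best guess correct |
|---|---|---|
| Fixed 4 | 31.6% | 70.2% |
| Random 4, 6 | 5.7% | 68.9% |
| Random 2, 4, 6 | 4.0% | 69.9% |
| Random 4, 6, 8 | 2.3% | 67.6% |

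Fixed 4 falls slightly below 33% and 71% here because 38 is not a multiple of 4.

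**What it could do to the result (assumption only).** Suppose staff shift the expected response by 5 points towards the known arm, and only when the next allocation is certain. The spurious difference is 2 × 5 × 0.333 = 3.3 points for size 4 and 2 × 5 × 0.20 = 2.0 points for size 8, against the planned 15. With 200 per arm and 60% response in both, the standard error is √(2 × 0.24 / 200) = 4.9 points. Those shifts are 0.68 and 0.41 standard errors, which take a two-sided 5% test to about 10% and 7%. If the shift is 2 points, size 4 gives 2 × 2 × 0.333 = 1.3 points, or 0.27 standard errors, and about 6%.

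If staff instead act on every best guess with the 5-point shift, the difference is 2 × 5 × (2g − 1), where g is the guess rate. That is 4.0 points for fixed 4 (g = 0.702) and still 3.5 points for random 4, 6, 8 (g = 0.676).

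**The case against.** The strongest reply is that the chain has unproved links. The article does not say who consents patients, who prepares or gives the infusion, or whether those people see or track earlier assignments. It gives no block size, which is consistent with withholding it, and whether sites are told is a detail that an article leaves to the full protocol. Staff would have to infer the size while following two separate sequences per centre. All of this stands, and it is why the point is a risk with moderate confidence.

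The core entry criteria are objective (haemoglobin range, laboratory values, ASA and ECOG), and chemotherapy need is balanced by design. That narrows the room for selection but does not close it, because the judgement-based exclusions remain.

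A reader might infer that small strata cause the problem. They do not: strata average 37.5 patients, and predictability comes from constant blocks run within one centre and stratum.

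A reader might also infer that the planned analysis could not reveal selective enrolment. The sample size section lists chi-square or Fisher tests for age, gender and clinicopathologic data, a t-test for haemoglobin before treatment, and a Z-test for follow-up. The baseline comparisons could show imbalance in measured factors, though they would not correct it or reach unmeasured ones.

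Finally, the remedy may come late. The first patient was randomised in January 2013, 400 were projected within a year, and the article appeared in April 2014 with recruitment still open. Few blocks may be left.

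**Conclusion.** The point holds as a weakness in a stated design choice. It is not a contradiction, a miscalculation or an omission that a fuller document would cure. Fixed blocks together with blinding described only for patients and outcome observers leave 33%, 25% or 20% of allocations knowable in advance for assumed sizes of 4, 6 or 8. This rests on three assumptions: site staff see past assignments in their stratum, they work out the size, and they take part in judging eligibility. None of these is stated in the article.

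A reader might conclude that enrolment was biased. The document does not show that, and the size of any effect depends on behaviour that nobody has measured. Nor should the 71% guess rate be read as a harm that varying block sizes would remove. The change should be made if blocks remain, with moderate confidence in the risk.

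**What to change.** For every block not yet opened, in all 12 strata, set the central system to draw block sizes at random, for example from 4, 6 and 8, and do not disclose the sizes to sites. Where existing staffing allows, keep past allocations from those who judge eligibility. This second step addresses the advantage from guessing, which varying the sizes leaves almost untouched.

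The system change itself is a configuration setting, and the endpoint and sample size stay as they are. The costs are a probable protocol amendment with local review at six centres, a slightly larger possible imbalance at the end of the trial, and little benefit if few blocks remain.

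### Randomisation is stratified by centre and chemotherapy need, but the only follow-up comparison named is an unstratified Z-test: mildly conservative if the strata predict response

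*Protocol article*

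**What the plan says.** Under Methods against bias, the article describes 1:1 block randomisation with fixed block sizes, stratified by each of six centres. It adds a second factor: "Further, patients will be stratified according to the need of adjuvant chemotherapy depending on the surgical/pathological stage".

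The section on sample size and statistical considerations names the tests. It opens with "The outcome parameters will be analyzed by a Pearson chi-square test or" Fisher's exact test, with a parenthesis listing age, gender, clinicopathologic data and morbidity. It assigns Student's t-test to pre-treatment haemoglobin and hospital days. The sentence closest to the primary comparison is "The Z-test will be used to determine whether or not a significant difference exists between two groups during follow-up". None of these is described as stratified or adjusted.

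The sample size comes from a two-proportion formula without strata: "with 90% power at a significance level of α = 0.05, 400 patients are required to be randomized".

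The Discussion expects that baseline haemoglobin may be lower in advanced cancer and calls for a subgroup analysis of those patients, motivated by quality of life. It gives no response rate by stage or by centre.

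**The concern.** Stratified blocks force the arms to be nearly balanced on centre and chemotherapy need. If those factors predict who gains 2 g/dl, the balance removes part of the chance variation in the difference between arms. A crude variance formula does not know this and still counts that variation. The standard error is then larger than it should be, the test rejects less often than its nominal 5% under the null, and precision that the design has already secured goes unused. How much is at stake depends entirely on how strongly the strata predict response.

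**Working it through.** **Inputs from the article.** Treatment response: "assuming a response rate to ferric carboxymaltose of 75% (per primary endpoint definition) by week 12". Control: "A response rate of 60% is assumed in the control group". α = 0.05, two-sided because the formula uses α/2; power 90%; allocation 1:1; six centres and two chemotherapy levels.

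**Assumptions, since the article gives no figures.** Two chemotherapy strata of equal size; a gap g in response between them, the same in both arms; a constant 15-point treatment difference; exact balance within strata. Crossing the two factors gives 6 × 2 = 12 strata, or 400/12 ≈ 33 patients each.

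**Step 1: the plan's own figure.** n per arm = (1.960 + 1.282)² × (0.60 × 0.40 + 0.75 × 0.25) / 0.15² = 199.6, so 200 per arm and 400 in total. The stated number reproduces with an unstratified formula.

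**Step 2: standard errors at 200 per arm.** The crude variance sum is 0.24 + 0.1875 = 0.4275, so SE = √(0.4275/200) = 0.04623 and the 95% half-width is 9.06 points. With responses p ± g/2 in the two strata, the average within-stratum variance in an arm is p(1 − p) − g²/4. Summed over both arms this is 0.4275 − g²/2.

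- g = 10 points: 0.4225, SE 0.04596, half-width 9.01, ratio √(0.4275/0.4225) = 1.006
- g = 20 points: 0.4075, SE 0.04514, half-width 8.85, ratio 1.024
- g = 30 points: 0.3825, SE 0.04373, half-width 8.57, ratio 1.057

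The ratio does not depend on n, so it also applies at 225 per arm.

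**Step 3: power.** The stratified test has power Φ(0.15/SE_strat − 1.96). The crude test has Φ((0.15 − 1.96 × 0.04623)/SE_strat), because its estimate varies with SE_strat while its threshold uses the crude SE. At g = 20 this gives Φ(1.363) = 91.4% against Φ(1.316) = 90.6%.

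**Step 4: type I error of the crude test.** With 67.5% response in both arms the crude variance is 0.675 × 0.325 = 0.2194, and the true one is 0.2194 − g²/4. At g = 20 the effective threshold is 1.96 × √(0.2194/0.2094) = 2.006, giving 4.5%.

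| Assumed gap (points) | Half-width crude / stratified (points) | Crude interval too wide by | Power crude / stratified | Crude type I error |
|---|---|---|---|---|
| 0 | 9.06 / 9.06 | 0% | 90.1% / 90.1% | 5.0% |
| 10 | 9.06 / 9.01 | 0.6% | 90.2% / 90.4% | 4.9% |
| 20 | 9.06 / 8.85 | 2.4% | 90.6% / 91.4% | 4.5% |
| 30 | 9.06 / 8.57 | 5.7% | 91.3% / 92.9% | 3.9% |

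**Step 5: cross-check by simulation.** The pooled Z-test was compared with a CMH test over 12 strata, with 400 patients, 20,000 trials per scenario for power and 60,000 for type I error. Power was 89.7% and 89.7% at no gap, 89.9% and 90.0% at 10 points, 90.4% and 91.2% at 20, and 90.6% and 92.5% at 30. A centre spread of ±5 points changed little: 90.5% and 91.3% at a gap of 20, 90.9% and 92.8% at 30. CMH kept its type I error at about 5% throughout.

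**The case against.** The strongest reply has three parts.

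First, this is a condensed article. No named test is tied explicitly to the primary endpoint, the Z-test sentence is generic, and an analysis plan that is not shown may specify a stratified method. That is fair as far as it goes: the text does not rule out a stratified analysis and is not self-contradictory. But the article does not stay silent. It names a between-group test, and that test does not use the randomisation strata. If the analysis plan is stratified, the published wording still needs to be brought into line.

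Second, nothing shows that the strata predict response. A lower starting haemoglobin in advanced cancer does not by itself mean that fewer patients gain 2 g/dl. The article gives the need for chemotherapy, not its timing, so treatment within the 12 weeks is also an inference. This stands, and it is why the effect is stated as a range that starts at zero.

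Third, the 400 patients were sized for a crude comparison, and the crude test delivers the target. This stands too. A reader might infer that the trial is underpowered or its result unreliable; the figures do not support that. Crude power stays at about 90% or slightly above across the range, and the error is conservative. A reader might also infer that a planned confidence interval is wrong, but the article mentions none for the primary endpoint. The interval widths above describe what a crude interval would be if one were reported.

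**Conclusion.** The point holds in a limited form. The design is stratified and the named follow-up comparison is not, which is a poor match. The consequence is conditional, conservative and small: nothing if the strata are not prognostic, under one power point for gaps up to 20 points, and about 1.6 (formula) to 2 (simulation) points at 30. What is forgone is a possible gain above the planned power. The size rests on the assumed gaps, equal chemotherapy strata, a constant risk difference and near-exact balance within strata. The direction needs only balanced strata that predict response.

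**What to change.** In the statistical section, state that the primary responder comparison is a CMH test stratified by centre and by the chemotherapy stratum as randomised, reported with a stratified risk difference and its 95% confidence interval. Keep the crude Z-test or chi-square as a supportive analysis. Fix this before outcomes are compared by arm, so that no choice between crude and stratified results arises later.

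The cost is wording only: both factors are needed to run the randomisation and so are available for the analysis. About 33 patients per stratum is enough for CMH, and in simulation it gave up no power when the strata were not prognostic (89.7% for both tests). Adjustment for baseline haemoglobin and an interaction test for the advanced-cancer subgroup are optional and not part of this point.
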